### Measures

#### Eligibility evaluation

At baseline and immediately post-intervention, participants will participate in a structured clinical interview to assess for psychiatric disorders (Mini International Neuropsychiatric Interview for DSM-5), past and current suicidality (Columbia Suicide Severity Rating Scale; C-SSRS), detailed medication and psychotherapy history, MRI safety, and history of head injuries (Ohio State University Traumatic Brain Injury Identification Method Short Form; OSU TBI-ID). Demographic information (e.g., age, biological sex, identified gender, sexual orientation, ethnicity, race, first language, education level, employment, handedness, marital status) will be collected via questionnaires completed by participants at baseline.

### Outcomes

#### AUD-related disability (primary)

The Drinker Inventory of Consequences (DrInC) assesses alcohol-related adverse functional consequences across physical (e.g., harmed physical health), interpersonal (e.g., loss of relationships), role responsibilities (e.g., missed work), psychological (e.g., loss of hobbies), and impulse control-related problems (e.g., legal problems); the first administration establishes lifetime consequences (DrINC-2 L) and a modified version of the DrInC-2R will be used to assess past 30-day consequences, and subsequent administrations assesses past 30-day consequences [48].

#### Recent alcohol and other substance use (secondary)

During each study visit, alcohol consumption will be quantified using the Time Line Follow-Back (TLFB). During this interview, participants are asked to report the number of days alcohol and other drugs were consumed as well as alcohol type,quantity, and beverage size using a calendar method. Percentage days heavy drinking ( > ≡ 4/5 drinks per single occasion for women/men) (PDHD) will be calculated as the TLFB outcome [49]. The TLFB will capture 90 days preceding the baseline appointment. At all subsequent visits, the TLFB will cover the time between interviews.

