### Sample size

Sample size determinations for the functional outcomes were made with a series of power calculations conducted using RMASS power calculation software for longitudinal mixed models. Parameters entered into the calculation included an effect size of d = 0.6 [32], 4 time points, attrition ranges between 20 and 25% based on rates in a prior VA-based clinical trial with a similar sample [47], and α = 0.05. Under the most conservative retention rate, we will need to enroll 136 participants to achieve 80% power. Sample size determinations for imaging outcomes were made using R:WebPower software for analysis of variance for a treatment group x time interaction term. Parameters entered into the calculation included an effect size of d = 0.80, 2 time points, and attrition as above with α = 0.05. We will need a sample of n = 51 to achieve 80% power to detect a treatment group x time effect on the regions encompassed within our a priori mask.

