## Outcomes and statistical methods

### Primary and secondary clinical outcomes

To evaluate whether AAT significantly improves clinical outcomes relative to Sham, a mixed effects model repeated measures (MMRM) model will be used. The dependent variable in the MMRM model is change from baseline in AUD-related disability (DrInC) at each post-baseline visit (post visit, 3 and 6 mo. follow-up). Predictors in the model will include treatment condition (AAT, Sham), visit (immediately post-training, 3 and 6 mo.), condition by visit interaction term, and baseline DrInC. The primary end point is the post-training visit. The same analytic approach will be applied to the secondary outcome (PDHD). We will model the distribution of percent days heavy drinking to ensure appropriate analysis. All subjects randomized will be included in the intent-to-treat analysis. Depending on the type of missing data, the appropriate statistical approach (e.g., multiple imputation) will be determined. Sensitivity analyses will be used to explore the impact of missing data.

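### The DrInC model adjusts only for baseline DrInC; pre-specifying the 90-day baseline PDHD as a second covariate may add modest precision at no data cost

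*Protocol article*

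**What the plan says.** The section on primary and secondary clinical outcomes specifies a repeated-measures mixed model for change from baseline in DrInC, with the post-training visit as primary endpoint. The listed predictors are treatment condition, visit, "condition by visit interaction term, and baseline DrInC". No other baseline measure is named. For heavy drinking it adds: "The same analytic approach will be applied to the secondary outcome (PDHD)". This implies adjustment for baseline PDHD alone but does not spell it out. The article also says that the distribution of PDHD will be modelled.

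Two instruments are scheduled for everyone at baseline (Table 1), and randomisation follows at the second visit (Allocation):

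- **Drinking calendar (TLFB):** "The TLFB will capture 90 days preceding the baseline appointment". PDHD is computed from it.
- **DrInC:** "the first administration establishes lifetime consequences (DrINC-2 L)", together with a past-30-day form. Follow-up forms cover 30 days, so a change score implies that the 30-day form is the baseline used in the model.

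The eligibility criteria admit participants with up to 90 days of abstinence.

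**The concern.** Baseline PDHD is a pre-randomisation measure closely related to the primary outcome, and it is already in the database. If it predicts post-training DrInC beyond baseline DrInC, leaving it out keeps removable variance in the standard error of the primary contrast.

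The protocol's own time windows give a reason to expect some added information. A participant who has been abstinent for 31 to 90 days may report few consequences over the last 30 days, yet show many heavy drinking days over the last 90. For that participant the model's one baseline covariate says least and PDHD may say most. The documents do not say how many participants will be in this position.

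What is at stake is power in a trial planned at 80%, not the validity of the test.

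**Working it through.** **Inputs from the Sample size section.** "Parameters entered into the calculation included an effect size of d = 0.6 [32], 4 time points"; "attrition ranges between 20 and 25"%; "and α = 0.05. Under the most conservative retention rate"; "we will need to enroll 136 participants to achieve 80% power". Sidedness is not stated; two-sided is assumed. Completers at 25% attrition: 136 × 0.75 = 102.

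**The plan's own figure.** A simple two-group formula at d = 0.6 gives 44 per arm, or 88 completers, and 88/0.75 rounds up to 118 enrolled in equal arms. That is not 136. A longitudinal test of group by linear time over four time points, with d = 0.6 at the last visit, attrition building to 25% and compound symmetry, gives 132 (equal spacing) or 138 (0, 1.5, 3 and 6 months) at a within-person correlation of 0.3. At 0.5 it gives 96 to 102, and at 0.2 it gives 150 to 156. The article states neither the correlation nor the tested contrast. So 136 is attainable but cannot be uniquely reproduced, and it is not shown to be wrong. The steps below start from the stated 80%.

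**Step 1: what baseline PDHD could add.** Let r1 be the correlation of post-training DrInC with baseline DrInC, r2 that of post-training DrInC with baseline PDHD, and r12 that between the two baselines. The share of remaining variance that PDHD explains is

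`partial R² = (r2 − r1·r12)² / [(1 − r1²)(1 − r12²)]`

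Using change rather than the raw score does not alter this once baseline DrInC is in the model. None of the three correlations is in the documents. Assumed values are r1 = 0.4, 0.5, 0.6; r2 = 0.2, 0.3, 0.4; r12 = 0.3, 0.5, 0.6, which makes 27 combinations.

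- Highest: r1 = 0.4, r2 = 0.4, r12 = 0.3 gives (0.40 − 0.12)² / (0.84 × 0.91) = 0.0784/0.7644 = 0.103.
- Middle: r1 = 0.5, r2 = 0.4, r12 = 0.5 gives (0.40 − 0.25)² / (0.75 × 0.75) = 0.04.
- Lowest: zero whenever r2 = r1·r12, for example 0.3 = 0.5 × 0.6.

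**Step 2: power and equivalent sample size.** With residual variance multiplied by (1 − R²),

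`power = Φ(2.80/√(1 − R²) − 1.96)`, `equivalent N = 136/(1 − R²)`

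| Partial R² | Power | Equivalent N |
|---|---|---|
| 0 | 80.0% | 136 |
| 0.02 | 80.8% | 139 |
| 0.05 | 82.0% | 143 |
| 0.10 | 84.0% | 151 |

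**Step 3: the cost.** With about 97 residual degrees of freedom, one more covariate multiplies the variance by about 97/96 = 1.010. Break-even is therefore a partial R² of about 0.01; 12 of the 27 combinations fall below it. Net of this cost, power is about 79.6% at R² = 0 and about 83.6% at R² = 0.10 (variance factor 0.90 × 1.010 = 0.909).

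This treats the post-training visit as a single covariate-adjusted comparison, which approximates the mixed model. It does not carry over to the PDHD model, whose distribution is left open.

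**The case against.** Adjusting a randomised comparison for the outcome's own baseline is standard and valid, and nothing in these sections is wrong or contradictory. The article does not claim that its list of predictors is exhaustive, and no SAP is shown. The more closely the two baselines are related, the more redundant the second tends to be. All of this stands, and it is why the point is one of efficiency, with a lower bound of zero. What remains is that the covariates are written out, so the choice can be examined, and that the 30-day and 90-day windows differ.

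Four stronger readings are tempting, and the documents support none of them:

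- **That precision is certainly lost.** No correlation is documented, and in much of the assumed range the gain is nil or slightly negative.
- **That power could reach about 88%.** This needs a partial R² near 0.20. One way to get there is r2 = 0.55 with r1 = 0.4 and r12 = 0.5, which gives 0.19. PDHD would then have to predict later DrInC better than DrInC's own baseline does.
- **That the missing-data assumption fails without PDHD.** The article names multiple imputation as one option and plans sensitivity analyses; baseline PDHD could enter there. Dropout that depends on baseline drinking equally in both arms would not bias the contrast in an additive linear model.
- **That the lifetime DrInC should be a covariate too.** No calculation supports this, and silence about its use in a condensed article is not a decision; it may be descriptive.

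**Conclusion.** The point holds as an optional efficiency improvement to a valid model. The DrInC model lists one baseline measure while a second, plausibly prognostic one is collected from everyone before randomisation, so precision at the primary endpoint may be given up. Before the covariate cost, the gain is 0 to about 4 power points from a nominal 80%, or 0 to about 11% in effective sample size (1/0.90 = 1.11). The possible loss is about 0.4 of a power point if PDHD adds nothing. These figures rest on the assumed correlations, a two-sided 5% test, about 100 completers and acceptance of the stated 80%. No bias is shown, and no size is claimed for the PDHD model.

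**What to change.** In the section on primary and secondary clinical outcomes, add 90-day baseline PDHD as a covariate in the DrInC model. By the same logic, add baseline 30-day DrInC to the PDHD model, in whatever distributional form is chosen. Keep the treatment, visit and interaction terms as they are. Fix the choice before unblinding, because covariates chosen after results are seen would undermine the primary test. While revising the sentence, state that baseline DrInC means the 30-day form.

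The cost is one sentence and about one degree of freedom per model, with no new data or visits.

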### Allocation

Randomization will occur during the second visit after eligibility criteria have been confirmed. Randomization sequences will be generated by the study quantitative psychologist, who is not involved in recruitment or data collection, using a computer-generated randomization sequence, using R (*Base* package*)* [50] and administered through RedCAPs randomization function. Randomization will occur without the ability to predict a participant’s allocation before randomizing. Randomization will be blocked (block size = 4 participants; 34 blocks total) and stratified by age category (2 strata: < 40 vs. > = 40 years old) given that age is known predictor of AAT response [31]. The study design will be double-blind, i.e., the participant, assessor, and PIs will be masked to the treatment condition for the duration of the trial with no planned unblinding. Within each stratum, participants will be divided into four groups, i.e., 2 treatment conditions (AAT vs. Sham) X 2 image set orders for Pre and Post Assessment AAT (AB vs. BA), with an allocation ratio of 1:1:1:1. Each computer program corresponding to each of the 4 conditions will be blinded such that the coordinator will not know the nature of the program. Assessors will not deliver the intervention. The patient and assessor will each rate their prediction regarding the patient’s assigned treatment condition after each assessment to check the success of blinding.

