### Procedure

Data collection is planned to take place between February 2023 and May 2026. Eligible participants will be enrolled in concert with clinical treatment initiation. Following a brief telephone screening, participants will complete a baseline visit that includes written informed consent, structured clinical interviews, and self-report questionnaires. At the time of consent, participants will be informed that they may refuse to participate or discontinue at any time and any participants wishing to withdraw will be given referrals for VA mental health services. If a participant expresses significant distress or discomfort during any procedures, the principal investigator will be notified and provide appropriate referrals or other clinical action. If eligibility is confirmed, participants will complete a second visit that includes the behavioral task (Alcohol Approach Avoidance Assessment). If participants are eligible to undergo fMRI scanning, they will complete the modified Alcohol Approach Avoidance Assessment while in the scanner. Training will be scheduled upon completion of visit 2. Participants will be scheduled to complete visits twice weekly for six weeks but will have up to 10 weeks to complete the 12 training sessions in the event of rescheduling. Immediately following the final training session, participants will complete two post treatment visits that mirror the first two assessment visits. Three months and six months after baseline, a research team member will administer the TLFB and assess treatment change. At these final two treatment follow-up appointments, participants will complete self-report questionnaires. See Table 1 for an outline of measures included in each appointment.

**Table 1 Tab1:** Measures by Visit

	Enrollment		Post-allocation			
Timepoint	Screening		Visit 2	Post	3-mo	6-mo

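### Post-training PDHD is counted from the visit 1 interview, so by Table 1 it includes days before randomisation at visit 2, which dilute the arm difference

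*Protocol article*

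**What the plan says.** The section on recent alcohol and other substance use sets two windows. For baseline: "The TLFB will capture 90 days preceding the baseline appointment". For later interviews: "At all subsequent visits, the TLFB will cover the time between interviews". It then makes the percentage of days heavy drinking the derived measure ("PDHD) will be calculated as the TLFB outcome") and names no subset of days.

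Table 1 marks the TLFB at the baseline visit, Post, 3 months and 6 months. The Visit 2 cell is empty. The Procedure section agrees: it describes visit 2 by the behavioural task, plus the scan for those eligible, and mentions no drinking interview.

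On the order of events, the Allocation section says "Randomization will occur during the second visit after eligibility criteria have been confirmed", and the Procedure section says "Training will be scheduled upon completion of visit 2".

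The statistical section models change from baseline at each later visit and takes the post-training visit as the primary time point for the DrInC. It then adds: "The same analytic approach will be applied to the secondary outcome (PDHD".

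**The concern.** An outcome compared between randomised arms should be built from time after randomisation. Here the post-training window opens at visit 1, when nobody has been allocated. Drinking between visit 1 and visit 2 cannot depend on the arm, so in expectation those days add the same amount to both arms. They enlarge the denominator of the percentage without adding to the difference.

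This does not depend on visits running late or on windows differing in length between participants. It happens when every visit is on schedule. For participants who attend Post, the 3- and 6-month windows open at a later interview and contain none of these days. The post-training estimate is therefore diluted and the later ones are not, which slightly tilts the condition-by-visit pattern for PDHD. A participant who misses Post would, under the same rule, carry the pre-randomisation days into the 3-month window.

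The outcome matters because reducing hazardous drinking is part of the stated primary aim, and PDHD is the measure of consumption that the article defines.

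**Working it through.** The article gives no figure for the interval from visit 1 to visit 2 or to the first session, and none for the expected PDHD effect. There is no stated figure to reproduce, so the size can only be shown as a range.

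**Inputs**
- T, days of training in the window: 42 (six weeks as scheduled) or 70 (the ten weeks allowed), from the Procedure section.
- a, days from visit 1 to randomisation at visit 2: not stated.
- b, days from visit 2 to the first session: not stated.
- g = a + b. The Intervention section has training begin in the participant's first week of outpatient treatment, and the Procedure section ties enrolment to the start of treatment. This makes g of about 7 days or less plausible but does not fix it. I use 3 and 7 days as assumptions.

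**Step 1: where the window opens.** The TLFB is at visit 1, there is none at visit 2 by Table 1, and the next is at Post. The Post window is then a + b + T days long, taking the post-training visit as directly after the last session.

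**Step 2: upper bound on dilution.** If the arms differ only during training, by an average of D points, the expected difference over the whole window is D × T/(T + g). The proportion lost is g/(T + g).

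| g (assumed) | T = 42 | T = 70 |
|---|---|---|
| 3 days | 3/45 = 6.7% | 3/73 = 4.1% |
| 7 days | 7/49 = 14.3% | 7/77 = 9.1% |

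As an illustration, a 20-point difference during 42 days of training would appear as 20 × 42/45 = 18.7 points at g = 3 and 20 × 42/49 = 17.1 points at g = 7.

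**Step 3: the part due to pre-randomisation days.** Days from visit 2 to the first session are after randomisation and belong in an intention-to-treat comparison. Relative to a window that opens at randomisation, the loss is a/(a + b + T). If, for example, 7 days split into a = 4 and b = 3, this is 4/49 = 8.2% with T = 42 and 4/77 = 5.2% with T = 70. It reaches the upper bound in Step 2 only if b = 0.

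**Step 4: the primary outcome.** The post-training DrInC asks about the past 30 days. Since 30 is less than 42, that recall period lies inside the training period and does not reach back to visit 1.

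**The case against.** **A TLFB at visit 2 may be intended.** The same section opens with "During each study visit, alcohol consumption will be quantified using the Time Line Follow-Back (TLFB". Visit 2 is a study visit, so read literally a TLFB is taken there and the next window opens on the day of randomisation. That would remove the problem. But it contradicts the empty cell in Table 1, and the Procedure section's account of visit 2 gives it no support. What stands is that the text and the table disagree and must be reconciled.

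**The interview rule may only govern data capture.** Leaving no gap in the calendar is sensible, and a full analysis plan might restrict the days that enter PDHD. That is possible. But the article states the window and makes PDHD the outcome of that interview, with no restriction. The point is about a stated rule that gives a worse result, not about a missing detail.

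**The effect is small and conservative.** This stands. Training is meant to begin in the first week of treatment, and the bias is towards no difference.

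**Stronger readings that the documents do not support.** A reader might assume gaps of two or three weeks and so a loss of a quarter to a third of the effect (14/56 = 25%, 21/63 = 33%). These sit poorly with the stated start of training. A reader might also convert the dilution into lost power using the d = 0.6 in the Sample size section. That effect size was entered for the functional outcomes, and the trial is not stated to be powered on PDHD. Finally, a reader might treat every day before the first session as wrongly counted. Only those before randomisation are.

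**Conclusion.** The point holds in limited form. With the TLFB schedule in Table 1 and the stated interview window, post-training PDHD includes pre-randomisation days, and these dilute the arm difference for any gap above zero.

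If visit 1 to first session takes 7 days or less, the dilution is at most about 14% with 42 training days and about 9% with 70, and less for the pre-randomisation part alone. This rests on the assumed gap and on there being no arm difference before training starts.

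The reach is narrow: one time point of one secondary outcome. A reader might infer from the primary end point wording that the primary result is at risk. It is not, because that end point is the DrInC, with its 30-day recall. No loss of power can be stated.

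**What to change.** - In the PDHD definition, state that post-training PDHD counts only TLFB calendar days on or after the randomisation date, by the same rule in both arms. Apply the same lower limit to the 3-month value when the Post interview was missed.
- State whether the days from visit 1 to visit 2 are excluded or added to the baseline window. Both use only pre-randomisation data, so either is acceptable.
- Reconcile the sentence that places a TLFB at every study visit with Table 1. If an interview at visit 2 is intended, mark it in the table; if not, limit the sentence to the visits that are marked.

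The TLFB is collected on a calendar, so this is a date filter on data already planned and needs no new visit. The downside is a slightly shorter post-training window, with a few fewer days per participant.

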#### Change in alcohol avoidance behavioral assessment (secondary)

Participants will complete a behavioral Alcohol Approach Avoidance assessment to measure automatic action tendencies to approach alcohol stimuli. Participants will see an alcohol or non-alcoholic beverage picture in the center of the screen framed by either a green or a blue border. They will be instructed to pull the joystick towards themselves when the border is green and to push the joystick away when the border is blue. When the participant pushes the joystick, the picture zooms out and when the participant pulls the joystick the picture zooms in, which creates the visual impression that the pictures are moving away or coming closer, respectively. Participants will be required to make an equal number of approach (pull) and avoidance (push) movements to both alcoholic and non-alcoholic drinks. To control for order and practice effects, there will be two sets alcohol and non-alcohol pictures (sets A and B), matched for beverage category, perceptual features, and national sales data characteristics, that are distinct from the stimuli used during training. Half of the participants in each condition will be presented with picture from set A at pre-test and pictures from set B at post-test (and vice versa). Reaction times are calculated based on the duration from the time the picture appeared on the screen to the time it disappeared. An approach bias score is computed by subtracting each participant’s mean response latency in the pull condition from their mean response latency in the corresponding push condition (e.g., alcohol-push minus alcohol-pull). The assessment block will comprise 128 trials: 16 Pictures x 2 Picture Type (alcohol vs. non-alcohol) x 2 Border Color (green vs. blue). Alcohol pictures include images of beer, wine, spirits, and mixed alcoholic beverages, each presented an equal number of times. The task outcome is change from baseline to post-intervention in behavioral approach bias score between baseline.

